### Randomization

The online randomization procedure will be carried out at the individual level. After returning the informed consent form and completing the baseline questionnaire, people who meet the inclusion criteria will be randomly allocated to the experimental group (Psyfit) or to the waiting list and they will be notified by email. Randomization will be stratified by gender, education, and severity of symptoms based on CES-D scores (scores between 10-15 and 16-24). A computer program will allocate participants using a generated randomization list. Block randomization in blocks of two will be performed to ensure equal distribution of participants across conditions.

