### Assessments

The primary outcome measure is well-being. Secondary outcome measures include depressive symptoms, general health and vitality, and economic costs (as measured by health care use, days of absence, inefficient job performance, and work productivity). For an overview of outcomes and instruments, see Table 1.

Measurements will be taken at baseline (pre-test), directly after the intervention (post-test, 2 months after baseline), and 6 months later (follow-up). All measurements are self-report measures and will be administered via email with a link to the questionnaire on the Internet.

High dropout rates are a characteristic feature of online trials and can be as high as 50% [50]. Therefore, email reminders and rewards (eg, raffle of six iPods and vouchers) for filling in the questionnaires will be used. It is expected that this will lead to a lower attrition rate.

**Table 1 table1:** Questionnaires and assessment times.

		T0	T1	T2
Questionnaire^a^	Measurement	Pre-test	Post-test^b^	Follow-up^c^
MHC-SF	Well-being/positive mental health	X	X	X
WHO-5	Well-being	X	X	X
CES-D	Symptoms of depression	X	X	X
MOS SF-36 subscales	Vitality and general health	X	X	X
TIC-P and PRODISQ	Health service uptake and production losses	X	X	X
CSQ-8	Client satisfaction		X	
Demographics	Age, gender, education, marital status, job status	X		

^a ^all questionnaires are discussed within Instruments section

^b ^2 months after T0

^c ^6 months after T0

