### Analysis

Results will be reported according to the Consolidated Standards of Reporting Trials (CONSORT) statement regarding eHealth [65,66]. We will adhere to the intention-to-treat (ITT) principle, which means all participants who have been randomized will be included in the analyses. Missing data at T1 and T2 will be imputed using the expectation-maximization (EM) method, as implemented in Statistical Package for the Social Sciences (SPSS) Missing Value Analysis. The program imputes missing values by maximum likelihood estimation using the observed data in an iterative process [67]. In online trials dropout is to be expected, and sometimes a large amount of missing data has to be estimated. Although ITT analysis is the approach of choice according to the CONSORT statement, there may also be pitfalls, such as when the missing-at-random assumption is not plausible and the results of the analysis are subsequently biased [68]. Therefore, a completers-only analysis and a per-protocol analysis will be conducted in addition (sensitivity analysis). Reasons for dropout in the study will be checked at random by telephone follow-up (dropout analysis).

To examine differences between the two conditions, we will use multiple regression analyses with the clinical outcomes on continuous measures (MHC-SF, WHO-5, CES-D, and the vitality and general health scales from MOS SF-36) as dependent variables and an intervention-control group dummy as predictor variable. We will compute standardized effect sizes (Cohen’s *d*). Cohen’s *d *is computed by subtracting the mean post-test intervention score from the mean post-test control group score and dividing the difference by the pooled standard deviation [69].

Moderator analyses will be conducted to examine which groups benefit more (or less) from the intervention by regressing the outcomes on independent variables such as gender, education, mild/moderate depressive symptoms, the treatment dummy, and the interaction with the treatment dummy and the selected independent variables.

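### The efficacy regressions name only the treatment dummy as predictor, so precision available from the baseline scores and the stratification factors is given up; the direction of Cohen's d also needs stating

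*Protocol article*

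**What the plan says.** Under Analysis, the protocol article introduces the between-group comparison: "To examine differences between the two conditions, we will use multiple regression analyses with the clinical outcomes on continuous measures". It lists MHC-SF, WHO-5, CES-D and the two SF-36 scales "as dependent variables and an intervention-control group dummy as predictor variable". That dummy is the one predictor named. Gender, education and symptom severity enter a model only in the next paragraph, which describes the moderator analyses.

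Under Randomization: "Randomization will be stratified by gender, education, and severity of symptoms based on CES-D scores", with CES-D bands of 10-15 and 16-24. The same section adds: "Block randomization in blocks of two will be performed to ensure equal distribution of participants across conditions". Allocation takes place after the baseline questionnaire has been completed, and Table 1 marks all the clinical outcomes at T0, T1 and T2.

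Cohen's d is obtained by "subtracting the mean post-test intervention score from the mean post-test control group score" and dividing by the pooled standard deviation.

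**The concern.** Two sources of precision are already built into the design: a baseline value of each outcome, and strata within which the arms are closely balanced. The efficacy model as worded uses neither. Leaving out the baseline value keeps variance in the residual that could be removed. Leaving out the strata means that the usual standard error does not reflect the balance that stratification has forced, so the test is conservative when the strata are prognostic. Baseline MHC-SF and WHO-5, the instruments for the primary outcome, are not stratification factors, so a chance imbalance on them is neither limited by the design nor corrected in the analysis.

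The effect-size formula is a separate and smaller matter. Subtracting intervention from control gives the same benefit opposite signs on the well-being scales and on CES-D, which makes a table of effect sizes easy to misread.

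**Working it through.** **Inputs from the article.** d = 0.33, alpha 0.05, power 80%, 145 per arm, 290 in total (Sample Size); two-sided tests (end of the analysis text); entry at CES-D 10-24 on a 0-60 scale and with moderate or low MHC-SF (Inclusion and Exclusion Criteria; Depressive Symptoms).

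**Inputs assumed.** The correlation r between the baseline and later value of an outcome, 0.2 to 0.7; the share R² of outcome variance explained by the strata, 5%, 10% or 20%. The article gives neither.

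**1. The article's own figure.** n per arm = 2(1.960 + 0.842)²/0.33² = 144.1, rounded up to 145, or 290 in total. Power at 145 per arm is 80.2% by the normal approximation and 80.0% by the noncentral t. The stated number is therefore correct for an unadjusted comparison of two means with complete data.

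**2. Adjusting for the baseline score.** The residual variance is multiplied by 1 − r², so the effective standardised difference is 0.33/√(1 − r²). For r = 0.5 this is 0.33/0.866 = 0.381. Noncentral-t power at 145 per arm with complete data:

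| r (assumed) | 1 − r² | Effective d | Power | d detectable at 80% power |
|---|---|---|---|---|
| 0 (as planned) | 1.00 | 0.330 | 80.0% | 0.33 |
| 0.2 | 0.96 | 0.337 | 81.5% | 0.322 |
| 0.3 | 0.91 | 0.346 | 83.5% | 0.314 |
| 0.4 | 0.84 | 0.360 | 86.3% | 0.302 |
| 0.5 | 0.75 | 0.381 | 89.9% | 0.285 |
| 0.6 | 0.64 | 0.412 | 93.8% | 0.263 |
| 0.7 | 0.51 | 0.462 | 97.5% | 0.235 |

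The last column uses the normal approximation.

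**3. Ignoring the strata.** Blocks of two within strata make the arms nearly equal on the stratification factors. If those factors explain a share R² of outcome variance, the true variance of the difference is (1 − R²) times what the unadjusted model reports. Actual type I error = 2[1 − Φ(1.96/√(1 − R²))]. For R² = 10%, 1.96/√0.90 = 2.066, which gives 3.9%. With k = 1/√(1 − R²) and 0.33 × √(145/2) = 2.81, power is Φ[(2.81 − 1.96)k] unadjusted and Φ[2.81k − 1.96] adjusted.

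| R² (assumed) | Actual type I error | Power, strata ignored | Power, strata in model |
|---|---|---|---|
| 5% | 4.4% | 80.8% | 82.2% |
| 10% | 3.9% | 81.5% | 84.2% |
| 20% | 2.8% | 82.9% | 88.1% |

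The gains in steps 2 and 3 overlap, because CES-D band is itself a baseline measure, and should not be added together.

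**4. Sign of d.** Take a benefit of 0.33 SD. On MHC-SF or WHO-5, where higher is better, control minus intervention gives (0 − 0.33)/1 = −0.33. On CES-D, where higher is worse, it gives (0 − (−0.33))/1 = +0.33. The formula refers to post-test means, and Table 1 uses post-test for T1 and follow-up for T2. The hypothesis covers both times.

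**The case against.** **The covariates may simply be unstated.** The article speaks of multiple regression, never says that the analysis is unadjusted, and condenses a fuller protocol. This is a fair caution about intent. But the article does state the model and its predictor, and it lists covariates in the moderator paragraph where it wants them. The label alone does not supply covariates for the efficacy model.

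**A reader might infer that the analysis is invalid or biased.** The article does not support that. Under randomisation the dummy-only comparison is unbiased, the sample size matches it, and omitting the strata makes the test conservative and does not inflate false positives. Blocks of two within strata also already limit imbalance on gender, education and CES-D band; the remark about chance imbalance stands only for baseline scores that are not stratified, notably MHC-SF and WHO-5.

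**The size of the gain is assumed.** This stands. Entry is restricted on CES-D and on MHC-SF, which tends to lower the baseline-outcome correlation on those scales. At r = 0.2 or 0.3 the gain is about 2 to 4 points of power.

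**It is tempting to quote the gain under dropout.** The Assessments section says that dropout in online trials can reach 50%. Power computed on the remaining participants describes only a completers analysis, whereas the main analysis includes everyone randomised with EM imputation. The figures here are therefore confined to complete data.

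**The sign of d might be read as contradicting the target of 0.33 or larger.** That goes too far. The Sample Size section describes the size of a difference to be detected, and the tests are two-sided. The sign changes no test, p-value or magnitude, and nothing in the article rules out a d at T2.

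**Conclusion.** The point holds as a matter of efficiency and of a conservative standard error. As written, the efficacy model forgoes a gain in power that ranges from about 2 points (r = 0.2) to about 18 points (r = 0.7) at 145 per arm, d = 0.33 and complete data; the lower values are plausible given the restricted entry scores. If the strata explain 5% to 20% of outcome variance, the nominal 5% test operates at 4.4% to 2.8%. Both ranges rest on assumed inputs. What does not depend on them is that the article stratifies on three factors, measures every clinical outcome at baseline, and names none of these in the efficacy model. The change is worth making, but validity is not in question. The direction of d is a minor reporting point.

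**What to change.** State that each efficacy model, at T1 and at T2, contains the treatment dummy, the baseline value of that outcome, gender, education and baseline CES-D. In the CES-D model, baseline CES-D is then both the outcome's baseline value and the severity covariate, and is entered once.

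Define d at T1 and T2 so that a positive value means benefit on every scale. Reversing CES-D alone does not settle this: the article codes vitality items from 1 (all the time) to 6 (never) and does not give the direction of the final SF-36 subscale scores, so that direction has to be stated first.

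The cost is a few sentences of analysis text, with no new data and no additional participants. Fixing the covariates in advance also removes a later choice between adjusted and unadjusted results.

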### The Current Study

The aim of this study is to evaluate the efficacy and cost-effectiveness of Psyfit, an online well-being program [39]. The study will add to the existing literature by testing a multi-component and flexible Internet-based intervention to promote well-being. To date, the research in this area is limited to either single interventions focusing on one well-being exercise at a time [28, 36] or to multiple protocol-based interventions [37,38]. In these studies, participants in the intervention groups are allocated to an inflexible intervention, although most people would prefer to choose what they need and feel up to doing [30,40,41]. For this reason, Psyfit offers a choice of different interventions that participants can tailor themselves.

The primary objective of this study is to evaluate the effectiveness of the Psyfit intervention in comparison to a waiting list control group. We hypothesize that the intervention group will demonstrate a significant increase in well-being and a reduction in depressive symptoms at post-test and follow-up compared to the control group. Secondary study objectives are to conduct an economic evaluation and to examine if particular subgroups benefit differently (ie, more or less) than others from the intervention.

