## Discussion

This online trial will examine whether an Internet-based self-help intervention for the enhancement of well-being is effective in terms of clinical outcomes and economic costs. A second objective is to examine whether certain groups benefit more or less from the intervention. The enhancement of well-being on a large scale may contribute to public mental health by resulting in better health, fewer mental disorders, and enhanced quality of life on a population level [11,70].

This study has several *a priori *limitations. First, dropout may occur in either of the two groups. To examine any selectiveness, we will conduct dropout analysis and a telephone survey for examining reasons for dropout. Moreover, we will conduct intention-to-treat analyses in which missing values are replaced by their most likely estimates. Second, we will only use self-report questionnaires, not formal diagnostic instruments, to establish diagnoses. Therefore, we will not know whether participants meet the criteria for a Diagnostic and Statistical Manual of Mental Disorders (DSM-IV) diagnosis so results about prevention of mental disorders will not be available. We opted for self-rating because the intervention should be easily accessible and highly applicable because of its public nature. We don’t want to scare people off by intensive diagnostic procedures. A third limitation of this study concerns the use of questionnaires that are not (yet) validated for online purposes. Psychometric properties of online assessments may differ from their paper-and-pencil counterparts [71]. On the other hand, the CES-D [45] and the MHC-SF [52], which are used in this study, have been proven to be reliable and valid instruments even if used on the Internet. Finally, the open recruitment strategy may attract certain groups, for example, more higher-educated people or more spiritually engaged and higher-motivated people. Therefore, care must be taken in generalizing the results.

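### Unless the EM imputation carries the treatment-by-moderator terms, moderator models run on EM-filled scores shrink interactions toward zero, by up to about the share of missing data

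*Protocol article*

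**What the plan says.** Differential benefit is a declared secondary objective. Under The Current Study the article undertakes to "examine if particular subgroups benefit differently (ie, more or less) than others from the intervention", and Study Design and Discussion repeat the aim.

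The Analysis section sets the route in three steps.

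- Imputation: "Missing data at T1 and T2 will be imputed using the expectation-maximization (EM) method", in the SPSS Missing Value Analysis module. The Discussion describes the result as "intention-to-treat analyses in which missing values are replaced by their most likely estimates", that is, one filled-in value per gap.
- Analysis set: "all participants who have been randomized will be included in the analyses".
- Moderator model: "Moderator analyses will be conducted to examine which groups benefit more (or less) from the intervention by regressing the outcomes on independent variables". The regressors are given as "independent variables such as gender, education, mild/moderate depressive symptoms", together with "the treatment dummy, and the interaction with the treatment dummy and the selected independent variables".

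The section also plans completers-only and per-protocol analyses as sensitivity analyses, because missing at random may not be plausible. It does not say whether these extend to the moderator models. It does not list the variables in the EM model or say whether EM is run separately by arm.

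**The concern.** EM for a multivariate normal model reproduces means, variances and pairwise linear associations. Suppose arm and moderator are both in the model but their product is not. A participant with neither T1 nor T2 observed then gets a predicted score in which the treatment effect is the same in every subgroup. The interaction survives only among participants whose scores were observed, and the regression on the filled data averages the two groups.

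This bias is in the point estimate. It does not depend on selective dropout, since it appears when data are missing completely at random. It is also separate from the understated standard errors of single imputation and from testing several moderators. Its direction is fixed: the more dropout, the more the trial appears to show that all groups benefit alike.

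**Working it through.** **Inputs from the article.** Sample Size: d = 0.33, 145 per arm, 290 in total, power 80%. Two-sided alpha is 0.05 (Sample Size; end of Analysis). Assessments: three waves, with dropout in online trials said to reach 50%.

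**Assumed inputs.** Missing share 10-50%; missing completely at random; a binary moderator split 50:50; wave-to-wave correlations 0.6-0.7; true interaction 0.40 or 0.50 SD. The article gives none of these.

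**The plan's own figure.** n per arm = 2(1.960 + 0.842)² / 0.33² = 2 × 7.85 / 0.1089 = 144.2, so 145. Power at 145 per arm is 80.2%. The figure is reproduced, but it is for the main effect only. For an interaction of 0.33 SD with complete data, SE = 4/√290 = 0.235, 0.33/0.235 = 1.40, and power is about 29%.

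**Expected shrinkage, plain EM (no product term, not run by arm).** Let p be the share missing.

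- T1, or T2 when the same people miss both waves: filled scores carry no interaction, so the share retained is 1 − p. This gives 0.90, 0.70 and 0.50 at p = 10%, 30% and 50%.
- T2 when T1 was observed: T1 passes on a fraction b of the interaction, where b is the regression coefficient of T2 on T1 given baseline. For equal interactions at both waves the share retained is (1 − p) + p·b. As an illustration, with correlations of 0.6 with baseline and 0.7 between T1 and T2, b = (0.7 − 0.36)/(1 − 0.36) = 0.53. The retained share is then 0.70 + 0.30 × 0.53 = 0.86 at 30% and 0.50 + 0.50 × 0.53 = 0.77 at 50%.

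**Simulation against that expectation** (share of the true interaction retained):

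| Setting | Plain EM | EM with product, or by arm with moderator | Completers only |
|---|---|---|---|
| Both waves missing, 10% | 0.90-0.91 | 0.99-1.01 | 0.99-1.01 |
| Both waves missing, 30% | 0.70-0.71 | 1.01-1.02 | 1.01-1.02 |
| Both waves missing, 50% | 0.50 | 1.00-1.01 | 1.01-1.02 |
| T2, 36% missing (20% at T1) | 0.74 | 1.01 | 1.01 |
| T2, 46% missing (10% at T1) | 0.74-0.75 | 1.01 | 1.02 |
| 20% control / 40% intervention | 0.66-0.71 | 1.02-1.03 | 1.03-1.04 |

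These rows use 200,000 simulated participants and a true interaction of 0.50 SD.

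A second simulation used N = 290, a true interaction of 0.40 SD, 600 trials per setting, and arm, moderator and baseline in EM. Mean estimates were 0.312, 0.271, 0.240 and 0.193 at 20%, 30%, 40% and 50% missing. Divided by 0.40, the shares retained are 0.78, 0.68, 0.60 and 0.48. A model on the observed scores gave 0.389-0.403. The overall treatment effect stayed at 0.33-0.34 against a true 0.33.

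A third simulation gave 0.91, 0.70 and 0.49 at 10%, 30% and 50% with both waves lost. With T1 observed it gave 0.87 and 0.76 at 30% and 50% missing at T2. The losses of 13% and 24% are a little under half the missing share. Adding the product restored 0.97-1.01.

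**Precision at N = 290, nominally 30% missing.** With the product added to single EM, the average model SE is 0.21 against a sampling SD of 0.26. Repairing the bias inside single imputation therefore leaves the test too liberal. Under plain EM the SE (0.212) matches the sampling SD (0.214), so there the damage is to the estimate.

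**The case against.** The strongest reply is that the article never gives the EM variable list. A reader might infer that the EM model omits the treatment-by-moderator terms. The document does not say so, and a condensed article may leave that list to a fuller protocol or an SAP. An analyst who adds product dummies, or runs EM by arm with the moderators included, follows the Analysis section to the letter and has no such shrinkage. This stands, and it makes the point conditional. It does not remove it: the article fixes the method and its use, and that method run plainly gives a biased answer to a stated objective.

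A reader might also infer that every interaction estimate loses the full missing share. That is too broad, because at T2 an observed T1 score carries part of the interaction and roughly halves the loss. Nor is 50% this trial's expected dropout. Assessments quotes it as an upper figure for online trials and expects reminders and rewards to lower attrition.

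The completers-only analysis would recover the interaction when data are missing completely at random. That is a real safeguard if it is applied to the moderator models, which the article neither states nor excludes. Even then, a gap between the EM and completers results could be misread as selective dropout when its cause is the imputation model.

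Finally, the practical weight is limited. At 30% missing and a true interaction of 0.50 SD, the loss of 0.50 × 0.30 = 0.15 is about 0.6 of the sampling SD (0.15/0.26). In that setting the test itself loses little against completers: 0.35/0.212 = 1.65 compared with 0.50/0.282 = 1.77. What suffers is mainly the reported size of the subgroup difference and its interval.

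**Conclusion.** The point holds conditionally. Unless the EM model contains the treatment-by-moderator products, or is run by arm with the moderators included, interaction estimates are pulled toward zero. The loss is up to about the missing share at T1, and at T2 when the same people miss both waves. It is about half that share at T2 when T1 was observed. Over an assumed 10-50% missing, the worst case is therefore a loss of roughly 10-50% of the true interaction.

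These sizes rest on data missing completely at random, a 50:50 moderator and the assumed correlations. The size of the true interaction is also assumed; the article plans none. The simulations give no ground for extending the point to the overall treatment effect, which was unaffected. The matter concerns a secondary objective that the trial was not powered for, but the correction is cheap and worth making before analysis.

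**What to change.** State in the Analysis section that the primary moderator models are not fitted to singly filled EM data, and choose one of two routes.

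1. Fit them by maximum likelihood to the observed T1 and T2 scores, in a mixed model with treatment × moderator × time and its lower-order terms. Enter the baseline score as a response, which keeps all randomized participants in the likelihood. Alternatively, enter it as a covariate and acknowledge that anyone missing both waves then contributes no outcome, which must be squared with the rule that all randomized participants are analysed.
2. Use multiple imputation, not single EM, with the treatment-by-moderator products in the imputation model, or impute by arm with the moderators included.

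In either case, say whether the completers-only and per-protocol analyses extend to the moderator models.

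The cost is wording and analysis time; no new data are needed. The visible downside is wider intervals than on singly filled data, because they reflect the information actually observed.

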**Conclusions:**

This study will examine the efficacy and cost-effectiveness of an online intervention that aims to promote well-being in people with elevated levels of depressive symptoms. If shown to be effective, the intervention could prove to be an affordable and widely accessible intervention to improve well-being in the general population.

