#### Depressive Symptoms

Depressive symptoms will be measured by the Dutch version of the Center for Epidemiological Studies Depression Scale, the CES-D [55]. The CES-D is a 20-item self-rating scale with item scores ranging from 0 to 3 (higher scores indicating more depression), and a total score from 0 to 60. The CES-D has acceptable reliability and validity with a cut-off score of 16 for mild depressive symptoms [42] and a cut-off score of 25 for severe depressive symptoms [56]. When applied via the Internet, the CES-D appears to be a reliable and valid instrument [45].

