### Sample Size

Depressive symptoms and well-being are used as a starting point for the power calculation. We aim to be able to show differences between Psyfit and the waiting list control condition with a standardized effect size (Cohen’s *d*) of 0.33 or larger. A standardized effect of 0.33 can be considered as the lower limit of a moderate clinical effect [64] and is based on a meta-analysis of well-being intervention research [35] and a recent randomized controlled trial [36]. To demonstrate this effect, and assuming an alpha of 0.05 and a statistical power (1-Beta) of 80%, we need 145 participants in each condition; therefore, we need 290 participants in total for the trial.

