The economic evaluation will be conducted from a societal perspective, thus including the intervention costs (ie, Psyfit), the costs of health care uptake (TIC-P), the participants’ out-of-pocket costs for obtaining health care (TIC-P), and the economic costs due to productivity losses in paid work (PRODISQ). The incremental cost-effectiveness ratio (ICER) will be calculated. Uncertainty in the ICER will be captured using a bootstrap approach, producing a scatter of simulated ICERs over the ICER-plane and by drawing an ICER acceptability curve of the likelihood that Psyfit is more cost-effective for a range of willingness-to-pay (WTP) ceilings.

All analyses will be conducted using two-sided tests and alphas of .05. For this purpose, the most recent version of the SPSS software will be used.

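### Baseline severity is to be tested as a mild/moderate grouping although a CES-D score is collected from everyone, and the only split in the protocol puts the lower group below its own cut-off for mild symptoms

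*Protocol article*

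**What the plan says.** The protocol article makes differential benefit by subgroup a secondary objective (The Current Study; Study Design). The Analysis section gives the method: regression on "independent variables such as gender, education, mild/moderate depressive symptoms, the treatment dummy" together with interactions between treatment and the chosen variables. It gives no cut-point for the severity groups.

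Four other places bear on what those groups are:

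- Randomization stratifies by gender, education and "severity of symptoms based on CES-D scores (scores between 10-15 and 16-24". No other CES-D split appears in the document.
- Depressive Symptoms gives the CES-D "a cut-off score of 16 for mild depressive symptoms" and a second cut-off of 25 for severe symptoms. It gives no boundary between mild and moderate.
- Inclusion and Exclusion Criteria describes the whole range 10-24 as running from very mild to moderate. The Abstract (Methods) describes the same sample as mild to moderate, without the very mild end.
- Table 1 shows the CES-D collected at baseline, so the numeric score is available as a moderator.

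**The concern.** There are two problems, and the first needs no calculation.

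**Labels.** If the moderator groups are the randomisation strata, the lower group (10-15) is below the score at which the protocol says mild symptoms begin. The upper group (16-24) holds everything from the mild cut-off to just under severe. A report that mild participants benefit more would then describe people whom the protocol's own scale places below mild. If a split within 16-24 was meant instead, the document gives no boundary for it, and participants scoring 10-15 belong to neither group.

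**Precision.** A score measured on 15 integer points is reduced to two levels. If the treatment effect changes steadily with baseline severity, this discards information that has already been collected.

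What is at stake is the answer to a secondary objective: which severity group a finding is attached to, and how precisely the trend with severity is estimated.

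**Working it through.** **Inputs from the protocol article**

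- Tests: "All analyses will be conducted using two-sided tests and alphas of .05" (Analysis).
- Design: "assuming an alpha of 0.05 and a statistical power (1-Beta) of 80" per cent, with a standardised effect "of 0.33 or larger" (Sample Size).
- Size: "we need 145 participants in each condition; therefore, we need 290 participants in total for the trial" (Sample Size).
- Strata 10-15 and 16-24 (Randomization); cut-off of 16 for mild (Depressive Symptoms).

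**Assumptions, not in the document:** the shape of the baseline CES-D distribution, linear moderation, no dropout, normal approximation, outcome SD = 1. The cut at 16 is inferred from the strata.

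**1. The stated sample size.** n per arm = 2(1.960 + 0.842)²/0.33² = 2 × 7.85/0.1089 ≈ 144.2, rounded up to 145. Power at 145 per arm is 80.2%. The figure reproduces, for the main effect.

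**2. Information kept by the split, uniform scores on the integers 10 to 24.**

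- Variance of the score = (15² − 1)/12 = 18.67, SD = 4.32.
- Share in 10-15 = 6/15 = 0.40. Group means are 12.5 and 20, a difference of 7.5 points.
- Correlation of score and split = 7.5 × √(0.4 × 0.6)/4.32 = 0.850.
- Information kept = 0.850² = 0.723, so the loss is 27.7%, or about 28%.

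**3. Other assumed distributions, same cut.**

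| Shape over 10-24 | Loss |
|---|---|
| Exponential decline | 26-28% |
| Linear decline | 27% |
| Truncated normal centred at 15.5-17 | 32-47% |
| Linear rise | 42% |
| Truncated normal centred at 19-22 | 45-51% |

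The uniform figure is near the low end of the range of about 26-51%.

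**4. Power for a difference of 0.33 SD between the effects in the two groups (uniform scores, N = 290).**

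- Split, with 58 and 87 per arm: SE = √(2/58 + 2/87) = 0.240. The ratio is 0.33/0.240 = 1.377, and power = Φ(1.377 − 1.960) = 28%.
- Continuous, same linear truth: slope = 0.33/7.5 = 0.044 per point. SE = 2/(√290 × 4.32) = 0.0272. The ratio is 1.619, and power = Φ(1.619 − 1.960) = 37%.
- Contrast detectable with 80% power: split 2.80 × 0.240 = 0.67 SD; continuous 2.80 × 0.0272 × 7.5 = 0.57 SD.

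**5. Sensitivity to the share in the lower group.** With 20%, 30%, 40% and 50% scoring 10-15, power with the split is 20%, 25%, 28% and 29%.

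**6. The same loss where power is otherwise adequate.** If the continuous test had 80% power, the split would have about 66% at 28% loss, 61% at 36% and 51% at 50%.

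**The case against.** The case on the other side is substantial, and several parts of it stand.

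- **The cut-point is not stated.** The Analysis section never says that the moderator is the randomisation stratum, and it lists the moderators only as examples. A condensed article may leave the coding to an analysis plan. This stands, so the point is conditional. It does not remove the label problem: neither available reading gives groups that the document's own cut-offs support as mild and moderate.
- **The loss figure is not in the documents.** This stands. It depends on an assumed distribution and on linearity. If the effect changed in a step at 16, the split would lose nothing.
- **The split is not the main cause of low power.** This stands. The continuous score moves power only from about 28% to about 37%. A reader might infer that splitting the score is what makes the subgroup answer weak, but the sample of 290 was sized for the main effect.
- **The sample is not misdescribed.** A reader might infer that the article hides participants below the mild cut-off. It does not: the eligibility criterion gives the range 10-24 and includes very mild symptoms, and Randomization gives the strata as scores. The Abstract's phrase "promote well-being in people with elevated levels of depressive symptoms" contradicts nothing, since no cut-off for elevated is defined.
- **A count of false positives is not supported.** A reader might multiply moderators, outcomes and time points into a fixed number of tests. The document does not fix the list of moderators or say that each is tested on every outcome and occasion. Multiplicity for secondary moderator analyses is commonly left to the analysis plan.

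**Conclusion.** The point holds in a limited form and is minor. The protocol groups a baseline score that it collects from everyone. If the groups are the randomisation strata, the lower one falls below the protocol's own cut-off for mild, so mild and moderate would be the wrong names. That conclusion rests on one inference, that the only split in the document is the one meant.

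The precision point rests on more: a cut at 16, roughly linear moderation and an assumed score distribution. Under uniform scores the loss is about 28%; across the shapes tried it is about 26-51%. Neither should be read as a property of this trial's data. The gain from the continuous score is real but modest, and the moderator question remains underpowered either way. The primary comparison is not touched.

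**What to change.** - Test the severity moderator as the interaction of treatment with continuous baseline CES-D, and plot the estimated effect across 10-24 to check linearity.
- Keep the 10-15 and 16-24 strata for stratification and description.
- Label the strata by score range, consistently with the eligibility criterion and the stated cut-off: 10-15 below the mild cut-off, 16-24 at or above it. Align the wording in the Abstract, Inclusion and Exclusion Criteria, Randomization, Depressive Symptoms and Analysis.
- Report the moderator results as exploratory estimates with confidence intervals.

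The cost is confined to analysis code and wording; no extra data are needed. The downside is that a single interaction term assumes an approximately linear change in effect with baseline score, which is why the plot belongs with it.
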